### Objectives and trial design

An RCT has been designed to evaluate the efficacy of autologous vBMA clots in SF procedures for patients with lumbar degenerative spine diseases. The study compares two groups: patients treated with autologous vBMA clots combined with bone allograft chips versus those receiving bone allograft chips alone (standard treatment). Additionally, the study assesses whether patient age and gender influence clinical outcomes.

As secondary objectives, this study aims to characterize platelet-specific parameters, cytokines/chemokines, growth factors, pro-inflammatory and anti-inflammatory markers, and MSCs that define the vBMA clot through molecular and cellular analyses. To further investigate its intrinsic biological potential, an advanced humanized three-dimensional (3D) *in vitro* SF model is developed. All experimental setups will consider age and gender differences, including an evaluation of their interactions.

Furthermore, the study examines the antibacterial properties of vBMA clot against common Gram-positive and Gram-negative bacteria associated with spinal infections, including methicillin-sensitive and methicillin-resistant *Staphylococcus aureus* and *Escherichia coli*. *In vitro* time-kill and bacterial adhesion assays are conducted to assess the ability of vBMA clot to inhibit bacterial growth as well as analyze the potential variations related to patient age and gender.

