### Outcomes

The primary outcome is to compare the two groups regarding the rate and duration of SF. Radiographic assessments are conducted preoperatively and at 1, 3, 6, and 12 months of FUs. To minimize exposure to ionizing radiation, computed tomography (CT) is performed only at 6 and 12 months, alongside x-rays. A diagnostic and interventional radiologist, blinded to group assignments, evaluates CT scans and x-rays, assigning interbody fusion grade according to the Brantigan classification (ranging from A to E, with E indicating the highest fusion rate) (22). The SF rate is analyzed over the FU period, considering variations due to age and gender differences.

The secondary outcomes include evaluating the pseudoarthrosis rate estimated using the Brantigan classification (22) and clinical outcomes. Moreover, since Brantigan (and other similar) classifications are visual qualitative scales affected by a lack of precise quantification, we provided a new quantitative analysis based on density calculated on CT images. The density of the selected region of interest (ROI) has been calculated and reported in Hounsfield Units (HU) for each study (baseline and follow-up controls). ROIs have been positioned within facet joint spaces of all vertebral levels of interest. Differential values in facet joint density have been reported by comparing baseline with follow-up controls to integrate the Brantigan scale (or help in cases of difficult grading selection), offering a quantitative and reliable tool. Measurements were performed using Picture Archive Communication System (PACS) software version 12.2.6.2000019.

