After defining and managing the dataset, bivariate or multivariate analyses are carried out to evaluate relationships between variables. In the case of continuous data, the independent Student’s *t*-test and Wilcoxon rank-sum test are used to compare data between the two treatments for parametric and non-parametric data, respectively. Linear models are applied for regression analysis. In the case of categorical dichotomous data, Fisher’s Exact test or chi-squared test is used to compare proportions between the two treatments, and logistic models are applied for regression analysis. For non-dichotomous categorical data, the Mann–Whitney U-test or the Wilcoxon rank-sum test is used to compare ordered outcomes between the two treatments, and the Ordinal Least Squares, Cumulative Link, or Multinomial Logistic models are applied for regression analysis.

Since the variable of the primary outcome is dichotomous (fusion or no fusion), it is analyzed in relation to age (categorized) and gender through logistic regression models. Additional factors (e.g., follow-up time points) and covariates (e.g., platelet-derived growth factors) influencing spinal fusion may be included in the model. To combine covariates into a multiple logistic regression model, collinearity and predictive power are assessed. The results are reported as odds ratios (ORs) with corresponding 95% confidence intervals (CIs). The primary outcome is also assessed through appropriate stratifications of the population based on the presence or absence of specific comorbidities.

Given the longitudinal nature of FU data (e.g., VAS, ODI, and spinal fusion grading across multiple time points), repeated-measures ANOVA or linear mixed-effects models are applied to assess both within-subject (time) and between-group (treatment) effects, accounting for intra-subject correlation and missing data. This finding allows for a robust evaluation of changes over time and treatment efficacy.

Finally, after defining the most reliable models based on multiple criteria (e.g., Akaike Information Criterion, R^2^), diagnostic tools are used to evaluate model assumptions and identify potential influential observations. The same analysis process is implemented for the other regression models related to secondary outcomes, with appropriate diagnostics applied.

Data collection and statistical analysis are standardized and blinded.

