### Scientific relevance and broader impact

The main challenge of SF surgery is to have a safe, functional, high-quality, and easy-to-use therapeutic strategy to improve surgery success and health-related quality of life, as well as in those patients with higher revision rates, such as female and elderly patients. The biological steps involved in creating a bony fusion between adjacent segments of the spine are a complex and highly coordinated series of events. In this context, the relevance of this research is to provide evidence on the potentiality of the vBMA clot as an autologous and multifunctional bioscaffold that can target all the main key challenges for SF surgery. First, the vBMA clot may act as an osteogenic and osteoinductive 3D bioscaffold containing pluripotent mesenchymal and hematopoietic stem cell that work synergistically to foster bone formation and regeneration. Second, platelet degranulation in the vBMA clot allows the release of various biomolecules (alpha granules, platelet-specific proteins, cytokines/chemokines, growth factors, coagulation factors, and adhesion molecules), which may promote early vascularization, a process vital for bone homeostasis, healing, regeneration, and the osseointegration of fixation hardware. Third, mesenchymal progenitors in the vBMA clot may modulate inflammation through a paracrine immunomodulatory effect, enabling an optimal transient stage of acute inflammation, which is a key element for successful bone healing. Fourth, an additional powerful element of the vBMA clot could be the critical role of the coagulation cascade and bone marrow MSCs in the early innate immune system activation and in their involvement in stressing and eliminating bacteria. The ability of the vBMA clot to provide a local combined delivery system of stem cells, signaling biomolecules, and anti-inflammatory and antibacterial factors, all enclosed by a matrix molded by the clot, represents an advanced and simple strategy to meet the main clinical needs of SF. vBMA is harvested simultaneously during the preparation of the site for pedicle screw insertion, and after clotting (~15–20 min), it is reintroduced in association with a bone allograft at the fusion site, without additional surgical time or donor site involvement. This approach offers a single, safe treatment while eliminating the need for *ex-vivo* cell manipulation, synthetic induction factors, or complex fabrication processes, thus providing a ‘One-Health’ strategy for SF surgery with a significant impact on patients.

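### The logistic model stated for the primary outcome names age and gender but not treatment arm, so an easy adjusted arm estimate is left to optional model selection

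*Protocol article*

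**What the plan says.** All references are to the protocol article.

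- **Outcomes** makes the primary question a between-arm one: "The primary outcome is to compare the two groups regarding the rate and duration of SF".
- **Statistical methods**, on the dichotomous fusion variable: "it is analyzed in relation to age (categorized) and gender through logistic regression models". This is the only regression written specifically for that outcome.
- The next sentence there leaves the rest open: "Additional factors (e.g., follow-up time points) and covariates (e.g., platelet-derived growth factors) influencing spinal fusion may be included in the model". Candidate covariates are then judged on collinearity and predictive power, and final models are chosen by criteria such as AIC and R².
- For dichotomous data in general, the same section says that Fisher's exact "test or chi-squared test is used to compare proportions between the two treatments, and logistic models are applied for regression analysis". It lists no terms for those logistic models.
- For longitudinal data, with fusion grading as one example, repeated-measures ANOVA or "linear mixed-effects models are applied to assess both within-subject (time) and between-group (treatment) effects". Age and gender are not named there.
- The primary outcome is also examined through "stratifications of the population based on the presence or absence of specific comorbidities", not by age or gender.
- **Objectives and trial design** sets the aim on age and gender: "the study assesses whether patient age and gender influence clinical outcomes". Interactions are mentioned only for the laboratory work.

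**The concern.** The randomised factor is missing from the one model that the article writes for the primary outcome. Its optional extras are illustrated by time points and growth factors, not by arm. If arm enters at all, it does so through a selection step based on predictive power and fit. The randomised factor should be fixed in advance.

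Two things are at stake:

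1. No adjusted arm effect is specified, although age and gender are baseline variables that the trial collects and models anyway.
2. The age and gender effects would come from a model that pools the arms and ignores what is planned to be a strong predictor of fusion.

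**Working it through.** **Reproducing the plan's sample size.** Statistical methods gives a control fusion rate of 0.70, an odds ratio of 4.8, a one-tailed Fisher test at 5%, power 0.80 and 20% dropout.

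- Experimental rate: 4.8 × (0.70/0.30) = 11.2; 11.2/12.2 = 0.918.
- The smallest n with exact Fisher power of at least 0.80 is 46 per arm (power 0.8015).
- Inflation: 46/(1 − 0.20) = 57.5, rounded up to 58. This matches the stated 58 per group.

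The trial is therefore sized on an unadjusted arm comparison.

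**What adjustment gains for arm.** Assumptions, none given by the document: 46 evaluable per arm, marginal fusion 91% vs 70%, standard-normal age, 55% women, two-sided likelihood-ratio tests. Three runs of 2,000 simulated trials per scenario gave these powers for the arm effect:

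| Age log-odds per SD | Unadjusted | Adjusted for age and gender | Gain (points) |
|---|---|---|---|
| -0.5 | 77 / 77 / 76.0% | 78 / 78 / 77.2% | 1 / 1 / 1.2 |
| -0.7 | 75 / 77 / 77.1% | 78 / 79 / 79.0% | 3 / 2 / 1.9 |
| -1.0 | 75 / 76 / 75.2% | 80 / 80 / 81.8% | 5 / 4 / 6.6 |

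The Monte Carlo standard error of one power is about √(0.8 × 0.2/2000) = 0.9 points, so the spread between runs is mostly noise. With no age effect there is no gain: 77.2% unadjusted, 77.0% adjusted. At 48 per arm (1,500 trials) the figures were 76.3% vs 75.9% with no prognostic effect, and 77.5% vs 78.2% with prognostic odds ratios of 2.

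**What including arm gains for age.** Same assumptions, two of the runs:

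| Age log-odds per SD | Power for age without arm | With arm | Gain (points) |
|---|---|---|---|
| -0.5 | 39 / 40% | 43 / 43% | 4 / 3 |
| -0.7 | 64 / 64% | 68 / 67% | 4 / 3 |
| -1.0 | 88 / 89% | 91 / 91% | 3 / 2 |

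**How precise an arm-by-gender (or arm-by-binary-age) term would be.** Assume subgroups of equal size and 91% vs 70% in each.

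- SE of the arm log odds ratio at n = 46: √[1/(46 × 0.91 × 0.09) + 1/(46 × 0.70 × 0.30)] = √(0.2654 + 0.1035) = 0.607.
- Each half-sample log odds ratio has twice that variance, and the interaction is a difference of two of them. Its SE is therefore 2 × 0.607 = 1.215. At 58 per arm it is 2 × 0.541 = 1.082.
- Power for a ratio of odds ratios of 4.8, two-sided 5%: Φ(ln 4.8/1.215 − 1.96) = Φ(1.569/1.215 − 1.96) = Φ(−0.67) = 25%. At 58 per arm it is 30%.
- Power for a ratio of 2: 8% at 46 per arm, 9% at 58.
- Ratio detectable with 80% power: exp[(1.96 + 0.84) × SE], about 30 at 46 per arm and 21 at 58.

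**The case against.** **Arm is unspecified, not excluded.** The list of extra factors is open. Logistic models are also mentioned directly after the between-treatment tests, and a mixed model with a treatment effect is named with fusion grading as an example. One can read the age-and-gender sentence as an addition to the arm comparison. A condensed article also commonly leaves model terms to a fuller document. This stands against any claim that the plan rules out an adjusted arm effect. It does not remove the point, because the article does write out a model for its primary outcome, and that model omits the randomised factor.

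**An unadjusted test is valid in a randomised trial, and the trial was sized on one.** This stands in full. The gain from adjustment is small, and every age slope used above is an assumption. The simulations also treat age as continuous, whereas the plan categorises it.

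**Stronger readings that the document does not support:**

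- *The pooled age coefficient would be biased by about 10%.* The gap to the arm-adjusted estimate is about that size, but it is non-collapsibility (marginal versus conditional odds ratio), not confounding. At 92 patients the pooled estimates average -0.49, -0.68 and -0.95 against true values of -0.5, -0.7 and -1.0, so 2 to 5% low. The adjusted ones average -0.54, -0.76 and -1.08, about 8% high.
- *The trial promises, but cannot deliver, an answer on whether the clot works differently in older or female patients.* The stated aim concerns the influence of age and gender on outcomes, which is a main-effect question. The remark in Scientific relevance and broader impact, "as well as in those patients with higher revision rates, such as female and elderly patients", describes the challenge of fusion surgery. It does not claim effect modification. The limit on answering that question is mainly sample size, as the interaction powers show.

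**Conclusion.** The point holds as an avoidable weakness in the stated model, not as an error in the main comparison. The primary outcome is a between-arm contrast, while the only regression written for it names age and gender, and inclusion of arm is left to optional, data-driven selection.

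The size is modest: roughly 1 to 6 points of power for arm under age slopes of -0.5 to -1.0 per SD (one run gave 6.6 at the steepest slope), none if age is not prognostic, and roughly 3 points for age. These figures rest on assumed slopes, continuous age and 46 evaluable patients per arm at 91% vs 70%. The case for changing the text is that the better model uses data already collected.

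**What to change.** In Statistical methods, state that fusion is modelled by logistic regression on treatment arm, age and gender, with arm always retained whatever the selection criteria show. Report the adjusted arm odds ratio with its 95% CI beside the unadjusted test.

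If statements about a different clot effect in elderly or female patients are intended, pre-specify arm-by-age and arm-by-gender terms. Add them one at a time, report them with 95% CIs, label them exploratory, and base such statements on nothing else.

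The cost is analysis wording only, with no new data or patients. The downside is that the interaction estimates will be imprecise: about 25 to 30% power even for a ratio of odds ratios of 4.8. The report must say so.

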### Statistical methods

The sample size for the trial was calculated through an *a priori* power analysis using G*Power software (version 3.1.9.6, University of Kiel, Germany), considering a power of 0.80 and a confidence level of 95% (one-tailed Fisher’s exact test). The effect size, in terms of odds ratio, was calculated based on spinal fusion literature data (23, 24). Ricart et al. (26) reported spinal fusion rates of 90% in patients treated with autograft + demineralized bone matrix (DBM), compared to 70% in those treated with allograft and bone marrow aspirate (BMA) (OR = 3.9). Slosar et al. (27) reported SF rates of 93% in patients treated with allograft and bone morphogenetic protein (BMP) compared to 73% of those treated with allograft alone (OR = 5.3). Therefore, the effect size was set at an OR of >4.8, assuming a higher SF percentage in the group treated with vBMA clot combined with allogeneic bone chips (>91%) compared to the group treated with allogeneic bone chips alone (<70%). For each treatment group, the minimum number of patients is *n* = 58, including a 20% drop-out rate.

Statistical analysis is conducted using R software and related packages, such as ggplot2, for graphical data representation. A *p-*value of < 0.05 is considered statistically significant. All data are recorded in an electronic dataset containing continuous variables (e.g., age, growth factor expression, and bacterial time kill results), categorical nominal variables (e.g., gender, diagnosis, and treatment), and categorical ordinal variables (e.g., Brantigan SF classification, VAS score, and ODI score). A univariate analysis should be conducted to determine the distribution, central position (e.g., mean and median), and dispersion (e.g., variance, standard deviation, and interquartile range [IQR]) of quantitative variables. For qualitative variables, frequency distributions are reported. Continuous variables with skewed distributions are transformed and assessed to achieve normality.

To prevent information loss and the introduction of potential selection bias, missing values may be imputed. In cases with very few missing values, a single imputation method is applied; otherwise, a multiple imputation method is applied, providing valid inferences under the missing at random (MAR) assumption. To perform multiple imputations, the Multivariate Imputation by Chained Equations (MICE) R package is used.

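### The plan allows visit as a factor in the logistic model for fusion without handling within-patient correlation, and assigns the repeated ordinal Brantigan grade to linear models

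*Protocol article*

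**What the plan says.** All statements are in the protocol article.

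- **Repeated readings.** Outcomes schedules postoperative radiographs at 1, 3, 6 and 12 months, with CT at 6 and 12 months only. It says the fusion rate is examined across follow-up, so each patient can supply up to four readings.
- **Binary outcome.** Statistical methods calls the primary outcome dichotomous and relates it to age group and gender by logistic regression. It then lists optional further terms: "Additional factors (e.g., follow-up time points"), alongside covariates such as growth factors. No random effect, GEE or clustered variance is named for this model. Results are to be odds ratios with 95% confidence intervals.
- **Longitudinal outcomes.** A later paragraph begins "Given the longitudinal nature of FU data (e.g., VAS, ODI, and spinal fusion grading across multiple time points") and names repeated-measures ANOVA or linear mixed models. It gives accounting for correlation within a patient as a purpose. These are the only methods in the section tied to that correlation.
- **Scale of the grade.** The same section lists "categorical ordinal variables (e.g., Brantigan SF classification, VAS score, and ODI score"). For ordered outcomes in general it names rank tests and a choice of regression models that includes cumulative link and multinomial models, with no repeated-measures form.

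**The concern.** The visit schedule is fixed, so visit can vary in a fusion model only if a patient contributes more than one record. A fused segment usually stays fused, so those records are positively correlated. Ordinary logistic regression treats each record as independent information. For anything that differs between patients rather than within them (treatment, age group, gender), the confidence interval is then too narrow and the p-value too small. Age and gender effects are stated study questions, and a treatment odds ratio from such a model would be affected in the same way.

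The one paragraph that does recognise within-patient correlation offers only models for continuous outcomes, and it names the fusion grade among its examples. A mean difference on grades A to E cannot be read as a fusion rate, nor as the odds ratio used to size the trial.

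**Working it through.** **1. The plan's own figure.** The inputs, from Statistical methods, are "considering a power of 0.80 and a confidence level of 95% (one-tailed Fisher’s exact test"), "the effect size was set at an OR of >4.8", and a control fusion rate of 70% (stated as below 70%).

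- Control odds: 0.70/0.30 = 2.333. Times 4.8 = 11.2. Experimental rate: 11.2/12.2 = 91.8%, consistent with the stated rate above 91%.
- Exact one-sided Fisher test at 0.05: 46 per arm gives power 0.801. Allowing for 20% drop-out, 46/0.8 = 57.5, rounded up to 58.

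The stated 58 per group is reproduced, with about 46 evaluable. That calculation uses one record per patient and is not at fault here.

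**2. Closed form for stacked records.** With k visits and common within-patient correlation ρ, the variance of a between-patient effect is understated by 1 + (k − 1)ρ, and the standard error by its square root. The true size of a nominal two-sided 5% test is 2[1 − Φ(1.96/√(1 + (k − 1)ρ))]. The range ρ = 0.3 to 0.9 is an assumption.

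| k | ρ | Variance factor | SE factor | True two-sided size |
|---|---|---|---|---|
| 2 | 0.3 | 1.3 | 1.14 | 8.6% |
| 2 | 0.9 | 1.9 | 1.38 | 15.5% |
| 4 | 0.3 | 1.9 | 1.38 | 15.5% |
| 4 | 0.9 | 3.7 | 1.92 | 30.8% |

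For a one-sided 5% test, the sidedness used for the sample size, the ranges are 7.5–11.6% (two visits) and 11.6–19.6% (four visits).

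**3. Simulation of the logistic model.** Fusion on treatment plus visit, no treatment effect, 48 per arm, 4,000 runs per scenario. Assumed fusion rates were 55% and 70% for two visits, and 10%, 30%, 55% and 70% for four. The correlation shown is between the last two visits.

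| Visits | Correlation | Model-based SE | Clustered SE | Size, model-based | Size, clustered |
|---|---|---|---|---|---|
| 2 | 0.32 | 0.305 | 0.351 | 8.8% | 4.8% |
| 2 | 0.47 | 0.305 | 0.370 | 10.4% | 5.2% |
| 2 | 0.65 | 0.305 | 0.393 | 13.4% | 5.0% |
| 4 | 0.32 | 0.237 | 0.315 | 14.3% | 5.4% |
| 4 | 0.47 | 0.237 | 0.341 | 17.0% | 5.0% |
| 4 | 0.65 | 0.237 | 0.364 | 20.0% | 4.9% |

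With zero correlation and two visits, both versions reject 5.0%, so the excess comes from correlation alone. The two-visit SE ratios agree with step 2: (0.351/0.305)² = 1.32, which is 1 + 0.32. The four-visit results fall below step 2 at the same nominal correlation. There, (0.364/0.237)² = 2.36 implies an average correlation of 1.36/3 = 0.45, less than the 0.65 between the last two visits.

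A second simulation, with 46 per arm and other assumed rates, gave 9.5–12.6% for two visits and 18.6% for four (5%, 20%, 50% and 70% fused). With clustered standard errors it gave 4.7–5.1%.

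**4. Linear model on the grade.** Assumptions: grades scored 1 to 5, fusion taken as the top two grades, cut-points 1.5 logits apart, and a constant proportional odds ratio of 4.8.

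| Control fusion | Mean grade, control | Mean grade, experimental | Difference |
|---|---|---|---|
| 10% | 2.15 | 3.07 | 0.93 |
| 30% | 2.94 | 3.87 | 0.93 |
| 55% | 3.57 | 4.38 | 0.81 |
| 70% | 3.93 | 4.61 | 0.67 |

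(Differences are taken before rounding.) A treatment effect that is constant on the odds scale shrinks on the mean-grade scale as grades approach the top. A linear model would show this as a treatment-by-time interaction. Under no effect, a linear comparison of patient mean grades over four visits (46 per arm, 10,000 runs) rejected 5.0%.

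**The case against.** The strongest reply is that the plan never says repeated readings will be treated as independent. Visit is an optional term. Stacking the records without clustering is inferred from silence, and an article may leave the variance estimator to an analysis plan that is not shown. The authors plainly know about within-patient correlation, since the longitudinal paragraph raises it. The sample size rests on Fisher's exact test, the proportions are compared by Fisher or chi-squared tests, and the logistic sentence is about age and gender.

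Much of this stands. A reader might infer that the primary treatment comparison will have about twice its nominal error rate. The document does not support that: a Fisher test or logistic model at one visit is untouched, and the inflation arises only if the multi-visit option is used as written. The bias also does not apply to every coefficient. For the visit effect itself, ignoring positive correlation tends to overstate the standard error.

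A reader might also infer that linear models on the grade raise the false-positive rate. Step 4 shows they did not. Such models on graded scores are a debated choice, the plan adds model diagnostics, and fusion proportions and odds ratios are reported anyway.

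The reply does not remove the point. The text offers visit as a term in a binary model, and the only correlation-aware methods it names are not models for binary or ordinal data. Assigning linear models to a grade that the same section calls ordinal is a stated choice, not an omission.

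**Conclusion.** The point holds in conditional form. If several visits per patient enter the logistic model without a correlation structure, nominal two-sided 5% for between-patient effects becomes roughly 9–13% with two visits and 14–20% with four. Clustering on patient restores about 5%. At the low end this is about 1.8 times nominal (8.8/5), so a blanket claim of at least a doubling would be too strong. The fusion rates by visit and the within-patient correlations are assumptions; the direction is the same across all values with positive correlation that were tried.

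The ordinal point is unconditional but milder: the linear analysis is on the wrong scale and its interaction term can mislead, while its type I error is sound. Both should be corrected before analysis. Neither affects the 58 per group.

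**What to change.** - Use one record per patient in any logistic model that has no correlation structure, and say which visit it uses.
- For any fusion analysis over several visits, use logistic GEE with patient-clustered robust standard errors, or a mixed-effects logistic model, with treatment-by-visit terms.
- For the repeated Brantigan grade, use a cumulative-link mixed model, and take fusion grading out of the sentence on ANOVA and linear mixed models.
- Keep the 1- and 3-month readings if they are wanted; handling correlation does not require dropping them.

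The cost is a wording change and standard R packages. Sample size, visits and data collection stay as they are.
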